##### Drug burden index

The drug burden index will be calculated for every patient. This drug burden index measures exposure to anticholinergic and sedative medication, and is associated with poorer physical and cognitive performance in older people [25]. Hence, the drug burden index can be seen as a proxy of drug therapy risk and medication safety.

##### Costs

A cost analysis will be performed, based upon reimbursement data from databases of a Dutch major health insurance company. Direct medical costs, such as for medication, hospital care, specialist care, diagnostic tests and other healthcare-related costs will be included.

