#### Group A: selecting GPs, non-dispensing pharmacists and matching both

General practices from the above mentioned networks are all pro-actively invited to participate in the POINT study. Ten general practices are selected, based on the following criteria: willingness of the GPs to participate in the project; willingness of the GPs to cooperate in the development and evaluation of the role of the NDP; minimum of 5000 registered patients; availability of an office for a NDP, with access to the GP information system; minimum of one practice nurse working on disease management programs for chronic conditions such as chronic obstructive pulmonary disease, diabetes, cardiovascular disease or mental health; healthcare centre accredited by the Dutch College of General Practitioners (NHG) [18]. The research collaboration is formalised in a collaboration agreement.

Ten non-dispensing pharmacists are employed, using a structured application procedure. All participating pharmacists have a master degree in pharmacy (PharmD) and preferably have working experience in providing pharmaceutical care to individual patients. Furthermore, in the selection procedure communication and collaboration skills, as well as pharmacotherapy knowledge, empathy, self-reflection skills and innovative attitude are emphasized.

Subsequently, each NDP is posted in one of the ten selected primary care centres in Utrecht or Amsterdam regions. The NDPs work full time and exclusively in the general practices, for a period of 15 months. The introduction of such a new role in a healthcare practice is complicated and faces a variety of challenges [14]. For example, pharmacists need to be trained to fulfil their new tasks, both pharmacists and GPs have to collaborate closely and GPs have to explore the complementary role of the NDP. Therefore, the first three months are used as a start-up period before actually starting the intervention period.

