#### Training program group A

To train the NDPs for their new role, a specialised Clinical Pharmacy Training Program (CPTP) is developed, based on workplace learning and the Canadian Medical Education Directions for Specialists (CanMEDS) Roles [21]. The CPTP started with a six-day training workshop, an internship in a nursing home and assignments in practice. Plenary education days are gradually decreased and days in the general practice gradually increased, ending with full time practice work with weekly education days at the university. Key elements of the training are consultation and communication skills, clinical reasoning, clinical pharmacotherapy and being reflective in practice. NDPs are trained to use a patient centred approach in providing care, instead of a drug product centred approach. Barriers to implementation are discussed and ongoing support is provided through structural intervision sessions and a mentorship and buddy program [22].

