#### Secondary outcomes

##### Potential medication errors

The percentage of patients with potential medication errors will be measured [24]. These potential medication errors mainly concern prescription errors, such as under- and overprescribing and dosage errors. Other potential medication errors might be due to medication that is not or insufficiently effective, or to inadequate monitoring of the effects of the therapy. Also administration errors, such as non-adherence problems, will be measured as potential medication errors. A complete list of included potential medication errors can be found in Table 2.

**Table 2 Tab2:** Overview of outcomes, measurements and data sources

Outcomes	Measurement	Data sources
*Primary outcome*		
Frequency of HARMs	Number of HARMs	DL, MH, MED
Secondary outcomes		
Potential medication errors	% patients with:	
	- medication not indicated	MED/MR
	- underprescribing	MED/MR
	- dosing error (too low or too high)	MED/MR
	- therapeutic duplication medication	MED/MR
	- medication contra-indicated	MED/MR
	- drug-drug interactions	MED/MR
	- medication not effective	MED/MR
	- inadequately monitored therapy	MED/MR
	- administration errors (e.g. non-adherence)	MED/MR
Drug burden index	Drug burden of medications with sedative and/or anticholinergic effects	MR
Costs	Medication costs and healthcare-related costs	Database of insurance company

HARM hospital admission related to medication, DL discharge letter, MH medical history (with ICPC codes for diagnoses), MED medication records (including ATC code, dose and strength), MR medical records (including laboratory markers and measurements such as blood pressure, pulse and body mass index)

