### Availability of data for secondary outcome measurements

To correctly measure and analyse the secondary outcomes, the required data need to be properly documented in the GPs’ information systems. Due to the heterogeneous study setting we are dependent on the diverse working methods of the participating healthcare providers. As this possible loss of information will show equally in each research arm, we expect this will not influence our study results.

The cost evaluation performed in this study will yield an insight in the direct medical costs of each model of pharmaceutical care provision in primary care. For this evaluation, a subgroup of patients will be analysed, as data of the insurance company will not be available for all patients. A full economic evaluation including a societal costs and economic modelling is outside the scope of this research project.

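### The cost comparison draws only on one insurer's claims; unless the NDPs are reimbursed there, model A is costed without its main added cost and looks too cheap

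*Protocol article*

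**What the plan says.** The Costs section of the protocol article gives the source: "A cost analysis will be performed, based upon reimbursement data from databases of a Dutch major health insurance company". It then describes the content: "Direct medical costs, such as for medication, hospital care, specialist care, diagnostic tests and other healthcare-related costs will be included". The costs row of Table 2 defines the measurement as "Medication costs and healthcare-related costs" and lists the insurance company's database as the only data source. Data collection adds that this insurer holds 40-55 % of the reimbursement data of the region.

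On the intervention, the section on selecting group A says: "Ten non-dispensing pharmacists are employed, using a structured application procedure". It continues: "The NDPs work full time and exclusively in the general practices, for a period of 15 months". The section on the group A training programme says that "a specialised Clinical Pharmacy Training Program (CPTP) is developed". None of these sections names an employer, a payer or a fee for NDP work.

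The Discussion, under availability of data for secondary outcomes, says the cost evaluation "will yield an insight in the direct medical costs of each model of pharmaceutical care provision in primary care". The limit on scope reads: "A full economic evaluation including a societal costs and economic modelling is outside the scope of this research project".

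**The concern.** The named source and the stated purpose do not fit together. Claims data record what an insurer paid for. The resource that distinguishes model A from models B and C is a full-time pharmacist in the practice, plus the training for that post. If neither produces a claim, the analysis counts any saving on drugs or admissions in group A and gives the means of achieving it a cost of zero.

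The pre-post design would not remove this. The NDP is present in group A only after the pre-intervention year, so the omission falls entirely on the group A change and passes in full into the comparison with B and C. Adjusting for baseline characteristics would not remove it either, because it is a missing component of the outcome and not confounding. Group A could then be reported as no more expensive, or as cheaper, only because its staffing was not counted.

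**Working it through.** The article states no cost figure, so there is no result to reproduce. The check has two parts.

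**1. Source against content**

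| Cost item | Named in the plan? | Source given |
|---|---|---|
| Medication, hospital care, specialist care, diagnostic tests | Yes | Insurer database |
| Other healthcare-related costs | Yes, as an open category | Insurer database |
| NDP employment (10 full-time posts, 15 months) | No | None |
| NDP training | No | None |

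The open category does not supply a second source, because both the Costs section and Table 2 base the analysis on the insurer's data. The scope limit removes societal costs and modelling. The pharmacist who delivers the care is neither; it is a direct cost.

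**2. Scale**

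Inputs from the article:
- Sample size calculation: ten practices and 45,000 patients per group, so 45,000 / 10 = 4,500 per practice.
- Sample size calculation: at least 2,850 high-risk patients per group, so 285 per practice. Check: 45,000 x 6.4 % = 2,880, close to the stated 2,850.
- Abstract: 5,000-10,000 patients per practice. The group A criteria set a minimum of 5,000.
- One full-time NDP per practice during the 12-month intervention period.

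Assumption, not in the article: EUR 60,000-90,000 per NDP-year, before training cost.

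Omitted cost per patient-year = annual NDP cost / patients per practice:

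| Denominator | At EUR 60,000 | At EUR 90,000 |
|---|---|---|
| 4,500 registered | 13.3 | 20.0 |
| 5,000 registered | 12.0 | 18.0 |
| 10,000 registered | 6.0 | 9.0 |
| 285 high-risk | 211 | 316 |

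A wider assumption of EUR 50,000-125,000 gives 50,000 / 4,500 = 11 to 125,000 / 4,500 = 28 per registered patient.

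The high-risk row charges the whole post to 285 people. It is an upper bound on the allocation, because the NDPs also run practice-wide quality work and see referred and self-referred patients.

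The direction needs no price. A positive cost that is missing from A alone lowers A's apparent cost.

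**The case against.** The strongest reply is that the article is silent on funding, and silence is not exclusion. It says only that the NDPs are employed. The cost list is illustrative and ends in an open category, and a condensed article may leave unit costs and allocation to a fuller document. This reply stands in part. A reader might infer that the NDPs are paid by the project and certainly absent from the claims; the article does not say so. That they are absent is the likelier reading for staff hired and posted for a 15-month study. The Background also reports that community pharmacists receive little or no fee even for existing medication reviews. The point therefore has to be stated conditionally. It is still more than missing detail, because the source is fixed in two places and does not match the purpose stated in the Discussion.

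A second reply is that a full economic evaluation is out of scope and that an analysis of reimbursed care answers a legitimate question. That is true of reimbursed care. It does not support describing the result as the direct medical costs of each model.

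A third reply is that pharmacist labour in B and C may also be only partly visible in claims, and that the certified review training in group B is not costed either. This stands and changes the remedy: adding costs to A alone would create a smaller imbalance the other way. It does not remove the concern, since no full-time post is added in B or C.

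Lastly, the euro amounts rest on an assumed salary, and the sample-size figure of 4,500 per practice lies below the article's own minimum of 5,000. Both are correct, which is why ranges are shown.

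**Conclusion.** The concern holds in conditional form. The only cost source named is one insurer's reimbursement data, and no claim is described for NDP work or training. Unless that work is reimbursed through this insurer, the cost comparison leaves out the main added cost of model A and favours A, while being presented as the direct cost of each model.

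Under the assumed EUR 60,000-90,000 per NDP-year, the omission is about EUR 13-20 per registered patient per year at 4,500 per practice, or about EUR 6-18 at 5,000-10,000. The documents support the direction; the amount rests on the assumed price.

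A reader might go further and call the NDP the main cost of model A overall. The article gives no cost figures, so this cannot be shown; the NDP is plausibly the main *added* cost. Nor does the point reach the primary outcome: medication-related admissions are counted independently of cost. This is a secondary-outcome issue of moderate severity.

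**What to change.** 1. State who employs and pays the NDPs, and whether any of that payment enters the insurer's claims.
2. If it does not, add NDP employment and training cost to group A from project records. Allocate it per registered patient, with allocation per high-risk patient as a sensitivity analysis. Divide by all registered patients, not only those in the insurer subgroup. If the practices mirror the region's 40-55 %, loading the full cost on the subgroup would inflate it by 1 / 0.55 = 1.8 to 1 / 0.40 = 2.5 times. State how the three start-up months are handled.
3. Treat additional pharmacist training and unreimbursed review work in groups B and C in the same way where known.
4. Report the comparison with and without these items.
5. If the costs cannot be added, label the outcome *reimbursed healthcare costs excluding the intervention* and make no claim about the cost of each model.

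The change needs no new patient data: only project records, whatever is known of pharmacist inputs in B and C, and a little extra analysis. The drawback for the sponsor is a figure less favourable to A.

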### Data collection

Data of all patients in groups A, B and C are accessible through the routine health care databases of the Julius General Practitioners Network (Utrecht) and the Academic Network of General Practitioners (Amsterdam). After the intervention period (see Table 1), key data will be extracted anonymously from the electronic medical records in the general practices of both the pre- and post-intervention period, through standard procedures and existing algorithms. These data (see Table 2) are combined with reimbursement data from the major healthcare insurance company in the Utrecht and Amsterdam region, obtaining 40-55 % of the reimbursement data of the region. No data will be obtained directly from patients.

### Confounding factors

To be able to control for possible confounding, characteristics of the involved general practices and pharmacies in each group will be collected, using a questionnaire. Additional information will be gathered about pharmaceutical care provision, the medication review protocol used, the setting of the pharmacy and the general practice, the collaboration between the pharmacy and the general practice and agreements on pharmaceutical care provision.

### Analyses and statistical method

All primary and secondary outcomes will be compared in pre-post analyses and between groups comparisons will be conducted. Descriptive statistics will be calculated for the baseline characteristics according to data of the overall population in group A, B and C, as well as for the high risk patients. The effect on the primary outcome will be tested with logistic multilevel analysis. The potential medication errors, drug burden index and costs will be tested with mixed effect models. Baseline characteristics can be integrated into the mixed effect models to control for confounding.

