## Methods

### Design

The POINT study is a non-randomised, controlled intervention study with pre-post comparison (see Table 1 for a time schedule of the POINT study). Three different models of pharmaceutical care provision in primary care will be compared:

**Table 1 Tab1:** Time schedule of the POINT-study

Period	Dates
Pre intervention period (1 year)	1^st^ of January 2013 – 31^st^ of December 2013
Start-up period, prior to intervention period (3 months)	1^st^ of March 2014 – 31^st^ of May 2014
Intervention period (1 year)	1^st^ of June 2014 – 31^st^ of May 2015

*Group A (intervention group)*: a GP practice with a non-dispensing pharmacist based in the practice as an integral member of the primary healthcare team;*Group B (control group 1)*: ‘upgraded’ care as usual: a GP practice collaborating with a dispensing pharmacist based in a community pharmacy in the traditional way, with the pharmacist having had a predefined, certified additional training in reviewing medication,*Group C (control group 2)*: care as usual: a GP practice collaborating with a dispensing pharmacist based in a community pharmacy in the traditional way.

A flowchart of the study design is shown in Fig. 1. Concurrently, a qualitative implementation study is performed.

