### Sample size calculation

With an expected prevalence of 4,5 % HARMs in 12 months within the high-risk population [26], we expect an effect of 50 % reduction of HARMs [1]. To show a statistically significant difference between the intervention group A and control group C, we include ten practices, with a total of 45.000 patients, in each group. As 6,4 % of patients in an average GP practice are part of the high risk elderly population [26], this means that in each arm at least 2850 high risk patients are included. This is based on an alpha of 0,05 and a power (1-beta) of 0,8.

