### Choice for the design

Despite the fact that a randomised controlled trial is the preferred design to evaluate the effect of an intervention, we thoughtfully chose to use a non-randomised model. In our opinion, willingness of all participating parties to improve pharmaceutical patient care is a key condition for the implementation of this intervention to succeed. This has been recognised before, during the implementation of a pharmacist in primary care in Canada [14]. Therefore, general practices participating in the intervention group of this study are selected instead of randomly allocated to one of three research arms.

This selection, of course, has disadvantages. Once proven effective, the broad implementation of this new function might be challenging because of the high standards we set for participating practices in this study. In addition, selection of motivated general practices might mask the effect of the intervention. As these practices are motivated to improve pharmaceutical care, standard pharmaceutical care might be better than average beforehand, leaving little room for improvement. By including pre-post analyses, we attempt to obviate this problem.

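### The plan does not make group A's pre-to-post change relative to group C's the primary effect, and it powers a one-period A-versus-C difference although practices were not randomised

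*Protocol article*

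**What the plan says.** The Design section describes the study thus: "The POINT study is a non-randomised, controlled intervention study with pre-post comparison". Table 1 sets the pre-intervention year as calendar 2013 and the intervention year as June 2014 to May 2015. Under Data collection, records are extracted for both periods in all groups.

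The Discussion (Choice for the design) explains that "general practices participating in the intervention group of this study are selected instead of randomly allocated to one of three research arms". It accepts that motivated practices may already give better care than average, and then says: "By including pre-post analyses, we attempt to obviate this problem".

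The section Analyses and statistical method contains three relevant sentences:
- "All primary and secondary outcomes will be compared in pre-post analyses and between groups comparisons will be conducted".
- "The effect on the primary outcome will be tested with logistic multilevel analysis". No model terms are given.
- "Baseline characteristics can be integrated into the mixed effect models to control for confounding". This adjustment is optional. It is worded for the mixed effect models, which that section assigns to the secondary outcomes.

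The Sample size calculation fixes one contrast: "To show a statistically significant difference between the intervention group A and control group C, we include ten practices". It uses a single 12-month risk of 4.5% and a 50% reduction, and no baseline period enters.

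**The concern.** The document names a selection bias and a remedy for it, but not the contrast that makes the remedy work. Pre-post data deal with a baseline difference only if A's change is set against the change in the controls. Taken singly, the two listed comparisons have different weaknesses:
- A pre-post comparison within A picks up anything that changed between 2013 and 2014-15, such as coding, admission policy or general prescribing practice.
- A post-period comparison of A with C picks up any difference that was already there in 2013.

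The only contrast with numbers attached, in the sample size section, is of the second kind. If that were the main analysis, a lower rate of medication-related admissions (HARMs) in A could be reported as a pharmacist effect when there is none. A true effect could also be hidden if A started higher than C.

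**Working it through.** **1. The plan's own figure.** Inputs from the Sample size calculation: 45,000 patients and 10 practices per group, a 6.4% high-risk share, 4.5% against 2.25%, alpha 0.05, power 0.80.
- Headcount: 45,000 × 0.064 = 2,880, which agrees with at least 2,850 per arm. Per practice: 2,850 / 10 = 285.
- Patients needed for a two-sided comparison of two proportions without clustering: n = [1.96·√(2·p̄·(1−p̄)) + 0.8416·√(p₁(1−p₁) + p₂(1−p₂))]² / (p₁−p₂)². With p̄ = 0.03375 this is (0.5006 + 0.2145)² / 0.0225² ≈ 1,011 per arm.
- Power at 2,850 per arm is 99.7% without clustering. It is about 80% only with an unstated design effect of 2,850 / 1,011 = 2.82, i.e. an ICC of (2.82 − 1) / (285 − 1) = 0.0064.

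That gap is a separate matter. The value 2.82 is used below only as one end of a clustering range.

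**2. False positives with no pharmacist effect.** The document gives no between-practice variation, baseline gap or trend, so these are assumptions: 10 practices per arm, 285 high-risk patients each, 4.5% base risk, practice SD 0.2 and practice-by-period SD 0.1 on the log scale. The simulation applies t-tests to practice-level results.

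| Scenario, no true effect | Post-only A vs C | Within A, pre-post | A-vs-C change |
|---|---|---|---|
| Equal baselines, no trend | about 5% | about 5% | about 5% |
| A starts 20% below C | about 25% | about 5% | about 5% |
| A starts 30% below C | about 52% | about 5% | about 5% |
| 20% fall in both arms | about 5% | about 30% | about 5% |

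The first two columns are nearly the same on the risk-difference and log-odds scales. The last column depends on scale once a gap and a trend combine. With A 30% lower and a shared 30% fall, the change contrast rejects about 8-9% of the time on raw proportions and about 5% on log odds.

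A simpler normal approximation gives the chance that a post-only test is significant in A's favour:
- 20% gap: 41% without clustering, 18% with design effect 2.82.
- 30% gap: 76% and 35%.

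**3. Power of the change contrast for a 50% effect.** In the simulation with equal baselines, power on the log-odds scale is about 88%, against about 95% for the post-only test. On raw proportions it is about 78% against 96%. If A starts 30% higher, the order reverses: about 91% for the change contrast against about 66%.

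A Wald calculation shows how far this depends on clustering. Take 2,850 per cell, 4.5% in three cells and 2.25% in A post-period:
- Effect: ln(0.045/0.955) − ln(0.0225/0.9775) = 0.716.
- Cell variance 1/[n·p(1−p)]: 0.00816 at 4.5% and 0.01595 at 2.25%.
- Simple contrast: SE = √(0.00816 + 0.01595) = 0.155.
- Change contrast: SE = √(3 × 0.00816 + 0.01595) = 0.201. The variance ratio is 1.68.
- No clustering, or clustering that cancels fully across periods: z = 0.716/0.201 = 3.56, power 94.5% (simple contrast 99.6%).
- Design effect 2.82 in every cell with no between-period correlation: z = 3.56/√2.82 = 2.12, power 56% (simple contrast 78%).

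**The case against.** The strongest reply is that the text is silent, not wrong. A controlled study with pre-post comparison is naturally read as comparing changes between groups. A logistic multilevel model can hold a group-by-period term, and exact model terms are commonly left to a full protocol or analysis plan, which is not shown. This stands as far as it goes: a reader might infer that the plan runs only separate comparisons and rejects the interaction, and the document does not say that. What it does not answer is that two statements in this document point the other way. The power statement fixes a one-period difference, and the Discussion presents pre-post analyses as the remedy without saying that the controls' change is subtracted.

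A reader might also infer a multiplicity problem of three pre-post and three pairwise tests, each at 0.05. The document sets out no such scheme. Alpha 0.05 appears only with A versus C, so one between-group contrast is singled out. What stays open is whether it is a post-period or a change contrast.

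Other handling is also planned: matching of B and C to A as far as possible on age distribution and socioeconomic status, collection of practice and pharmacy characteristics, and optional baseline adjustment. These reduce bias, so it would be too strong to say that only a change contrast can help. None of them measures the prior HARM rate or the motivation on which A was selected.

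Finally, the Discussion's stated worry is good prior care that leaves little room to improve. That is a ceiling problem, and a change contrast does not cure it.

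**Conclusion.** The point holds in this form: the protocol does not state that the primary effect is the A-versus-C difference in pre-to-post change, and it bases power on a simple one-period difference that is open to the selection it acknowledges. It does not hold as a claim that the plan excludes the interaction.

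The false-positive rates of about 25-52% (post-only, 20-30% baseline gap) and about 30% (within A, shared 20% fall) rest on assumed gaps, trends and practice variation. They show the size of the exposure and do not estimate what happened. The figure of about 5% for the change contrast is safe across the scenarios shown on the log-odds scale, which fits the planned logistic model. The contrast removes fixed baseline differences and shared trends only. It still assumes that A and C would have moved in parallel, which practices selected for motivation may not do.

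**What to change.** In the analysis section, name one primary test: the A-versus-C group-by-period term (2013 against June 2014 to May 2015) in the planned logistic multilevel model. Fit the model to both periods, with random effects for practice and for practice-by-period. Report within-arm changes descriptively. State in the Discussion that the remedy for selection is this contrast, and that it relies on parallel trends. Restate the power for this contrast with the assumed ICC and between-period correlation.

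No new data are needed, because both periods are already to be extracted. The cost is lower power than a post-only test when baselines are equal: about 88% against 95% under the assumed inputs on the log-odds scale, and 56-95% across the clustering assumptions above.
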